### Laboratory investigations

Venipuncture will be performed on the median cubital vein of participants, and blood samples will be collected into evacuated tubes by using aseptic precautions. Urine samples will also be drawn into standard urine collection containers. All biochemical analyses, except adiponectin, will be performed in the Seoul National University Hospital Department of Laboratory Medicine, a fully accredited diagnostic laboratory. Specifically, the department of laboratory medicine of our institute is accredited by the College of American Pathologists (CAP) and has been inspected every 2 years since 2012. The proficiency testing offered by CAP has been performed for all laboratory assays, including hemoglobin A1c. With regard to the details of hemoglobin A1c measurement, venous blood samples collected in ethylenediaminetetraacetic acid bottles will be transported immediately from outpatient clinics to the department of laboratory medicine. Then, hemoglobin A1c will be measured using ion exchange high-performance liquid chromatography (VARIANT II TURBO 2.0 system; Bio-Rad Laboratories, Hercules, CA, USA). Patients will be requested to be fasting for > 10 h prior to the test, although hemoglobin A1c values reflect the average glucose level over the last several weeks. The within-laboratory coefficients of variation for the hemoglobin A1c assay are 1.26% for the normal quality control material and 0.85% for the high quality control material, respectively, representing excellent within-laboratory replication. Analysis of adiponectin will be performed at GreenCross LabCell Corp. (Yongin, Korea), an established diagnostic laboratory certified by the key domestic and international accreditation bodies, including CAP. Adiponectin will be measured by enzyme-linked immunosorbent assay (ELISA) (Human Adiponectin ELISA, BioVendor, Brno, Czech Republic; VersaMax ELISA Microplate Reader, Molecular Devices, Sunnyvale, CA, USA). Samples will be stored at −70 °C because the analysis of adiponectin will be performed as a batch, whereas other biochemical analyses will be conducted as patients present.

### Trial organization

The executive committee, composed of the study chairperson and selected members among the investigators, will govern all aspects of the LESS-DM trial. This committee will also be responsible for reviewing the final results, determining the methods of dissemination, and preparing the subsequent publications. Data coordination will be conducted at the Cardiovascular Center of Seoul National University Hospital. The data and safety monitoring board, composed of cardiologists and a biostatistician, will be responsible for making recommendations on any issue related to the safety or compliance of the patients throughout the course of the trial. This board will be able to recommend that the executive committee stop the study prematurely or modify the study protocol, although all final decisions regarding these issues will rest with the executive committee. The study sponsor, JW Pharmaceutical Corporation (Seoul, Korea), will only provide funding for this trial and will not have access to the study results until the final analyses are completed.

### Data and safety monitoring plan

The investigators and clinical research coordinators will regularly monitor all parts of the trial, including the enrollment status, medical records, case report forms, and compliance with the study protocol, during the study period. For safety evaluation, adverse events will be assessed and reported during each patient visit. All serious adverse events will be reported to the investigators and the ethics committee.

### Personal data protection and confidentiality

Confidentiality will be maintained throughout the trial by assigning all participants with a unique identification code. In order to protect participants’ anonymity, their names will not be used. The files containing the personal details of the participants along with their identifier codes will be stored separately in a locked filing cabinet and will be accessible only to the principal investigator. All data will be kept for a maximum of 3 years from the date of completion of this study and then destroyed securely.

### Sample size

The sample size was calculated by assuming an expected difference of 0.2% in hemoglobin A1c change between the groups and a population variance of 0.5%, based on previous studies [25, 26]. Thus, with a power of 95%, a two-tailed α of 5%, and a presumed dropout rate of 10%, a sample of 250 patients in each group will be sufficient to detect this difference. Accordingly, a total of 500 participants will be randomized and included in our analysis.

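### The stated 95% power does not follow from the stated inputs: 225 evaluable per group gives about 85% if 0.5 is a variance and about 99% if it is an SD

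*Protocol article*

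**What the plan says.** The Sample size section gives a complete set of inputs. The calculation is described as "assuming an expected difference of 0.2% in hemoglobin A1c change between the groups", with "a population variance of 0.5%, based on previous studies". The remaining inputs and the result are "with a power of 95%, a two-tailed α of 5%, and a presumed dropout rate of 10%, a sample of 250 patients in each group". The section states that "a sample of 250 patients in each group will be sufficient to detect this difference", and the total is 500 randomised.

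Two other sections bear on the calculation. Randomization gives 1:1 allocation. Statistical analyses says that the difference in changes will be compared with both Student's t test and analysis of covariance on the baseline value. No correlation between baseline and follow-up, and no other reduction of the variance, is given anywhere.

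**The concern.** A sample-size statement that gives difference, spread, alpha, power and dropout should reproduce its own N, and this one does not. The spread is also ambiguous. It is called a variance but carries a percent sign, the same unit as the 0.2% difference, so it could be an SD. The two readings put the trial on opposite sides of the stated power.

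The power concerns the only primary endpoint, the change in HbA1c at 24 months. The section on strengths and weaknesses concedes that the trial is small for clinical outcomes and for subgroup analyses, so the HbA1c comparison carries the conclusion. A reader who trusts the 95% would take the risk of missing a true 0.2-point difference to be 5%. On the literal text that risk is about three times as large.

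**Working it through.** **Inputs.** From Sample size: difference d = 0.2; spread 0.5, called a variance; two-sided alpha 0.05; power 95%; dropout 10%; 250 per group. From Randomization: 1:1 allocation. Evaluable per group after dropout: 250 × 0.9 = 225.

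**Formula** (two independent means, normal approximation): n per group = 2 × (z₀.₉₇₅ + z_power)² × variance / d², rounded up, then divided by 0.9 and rounded up for dropout.

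**Attempt to reproduce 250 at 95% power.** (1.960 + 1.645)² = 12.995.

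- Variance 0.5: 2 × 12.995 × 0.5 / 0.04 = 324.9, so 325 evaluable; 325/0.9 gives 362 randomised per group, 724 in total. The plan is 112 per group short.
- SD 0.5 (variance 0.25): 2 × 12.995 × 0.25 / 0.04 = 162.4, so 163 evaluable; 163/0.9 gives 182 randomised per group, 364 in total. The plan is 68 per group over.

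**Other conventions, at 95% power.**

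| Variant | Evaluable per group | Randomised per group |
|---|---|---|
| One-sided alpha 0.05, variance 0.5 | 271 | 302 |
| One-sided alpha 0.05, SD 0.5 | 136 | 152 |
| Dropout added as n × 1.1, variance 0.5 | 325 | 358 |
| Dropout added as n × 1.1, SD 0.5 | 163 | 180 |
| One-sample formula, variance 0.5 | 163 | – |
| One-sample formula, SD 0.5 | 82 | – |

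None gives 250.

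**Which power gives 250?** With variance 0.5, two-sided alpha 0.05 and 10% dropout:

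| Power | Evaluable per group | Randomised per group |
|---|---|---|
| 80% | 197 | 219 |
| 85% | 225 (224.46 before rounding) | 250 |
| 90% | 263 | 293 |
| 95% | 325 | 362 |

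**Power of the planned design.** Power ≈ Φ(d / √(2 × variance / n) − 1.960).

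- Variance 0.5, n = 225: standard error √(1/225) = 0.0667; 0.2/0.0667 = 3.00; Φ(1.04) = 85.1% (noncentral t: 84.9%).
- SD 0.5, n = 225: standard error √(0.5/225) = 0.0471; 0.2/0.0471 = 4.24; Φ(2.28) = 98.9% (noncentral t: 98.9%).
- All 250 per group analysed: 88.5% (variance 0.5) or 99.4% (SD 0.5).

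**What would make 95% true at 225 evaluable?** Either an SD of 0.588 (variance 0.346) with d = 0.2, or a difference of 3.605 × 0.0667 = 0.24 with variance 0.5. The section states neither.

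**The case against.** The strongest defence is that the percent sign marks the 0.5 as a loosely worded SD. The design is then conservative: 182 per group are needed, 250 are planned, and the claim that 250 suffices is true. That is a fair reading, but 250 is still not what 95% power gives. On the literal reading, as a variance, the claim of sufficiency is false.

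A second defence is that analysis of covariance is planned and could reduce the variance. With variance 0.5, a correlation with baseline of about 0.55 gives 2 × 12.995 × 0.5 × (1 − 0.55²) / 0.04 ≈ 227 evaluable. Alternatively, a cross-sectional SD of 0.5 with a pre/post correlation of about 0.3 gives a variance of change of 2 × 0.25 × 0.7 = 0.35 and 228 evaluable. Both come close to 250 randomised. Neither correlation is stated, and the section describes a plain difference in change, so these remain possible explanations that the document does not support.

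A third point is that the main analysis is by intention to treat and all 500 are to be included. With 250 analysed per group, power on the literal reading rises to 88.5%. The gap narrows but does not close.

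Two cautions stand. The slip from 85% to 95% is an inference from an exact numerical match, not something the document shows. And the reading of a null result will rest on the confidence interval and the observed SD more than on planned power, so the error distorts the assessment of the design and does not make the result unreadable.

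**Conclusion.** The concern holds. Difference, spread, alpha, power, dropout and N are mutually inconsistent under both plain readings of the 0.5, and no other section reconciles them. With 225 evaluable per group and a true difference of 0.2, the chance of missing it is about 15% if 0.5 is the variance and about 1% if it is the SD, against the stated 5%. If 0.5 is the variance, the difference detectable with 95% power is 0.24, not 0.20.

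These figures assume a two-sample comparison of change, equal groups, 10% loss and no baseline adjustment. The mismatch is certain. Its cause is not, although 85% power with variance 0.5 is the only plain combination found that returns exactly 250. Because this is the headline power for the primary endpoint and the correction is cheap, it must be fixed.

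**What to change.** Return to the calculation behind the 250 and to the source of the 0.5, keep N = 500, and correct the sentence in Sample size:

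- If 0.5 is the variance: *SD of change 0.71 percentage points (variance 0.5); 225 evaluable per group gives 85% power for a 0.2-point difference; 250 randomised per group allows for 10% dropout.*
- If 0.5 is the SD: call it an SD of 0.5 percentage points and restate the power as about 99%.
- If another SD (about 0.59) or a baseline correlation was used: state it and its source.

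In every case give the unit of the spread. The cost is one sentence and no more patients, though the stated power may become less favourable. Only if 0.5 really is the variance and 95% power is to be kept would N have to change, to 724 in total on these inputs; that choice belongs to the trial team.

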### Statistical analyses

The statistical analyses will be performed on both intention-to-treat and per-protocol bases. The intention-to-treat analyses will include all randomized participants who provide written informed consent, regardless of whether the study treatment is administered correctly. The per-protocol analyses will include all study participants who complete the trial with an adequate administration of the study drug (≥70% of the planned doses) and without any major protocol violations. Major protocol violations include inappropriate enrollment, the use of a prohibited concomitant medication, a violation of the dose or schedule of drug administration, or any other violation considered to be a major violation. The main analyses will be performed on an intention-to-treat basis.

The values will be expressed as the mean ± SD or median (IQR), as appropriate. Comparisons of continuous and categorical data will be made by Student’s *t* test and the chi-square test, respectively. The difference in changes between the groups will be analyzed using both Student’s *t* test and analysis of covariance to adjust for the baseline values. Two-sided *p* values < 0.05 will be considered statistically significant. All analyses will be performed using IBM SPSS version 22.0 software (IBM, Armonk, NY, USA).

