## Discussion

The risk of statin-induced diabetes has been found to be increased in patients receiving an intensive statin regimen and in patients with known risk factors for NOD [5, 6]. Hence, patients at high risk for developing NOD, such as patients with MetS, should be monitored carefully, particularly when high-intensity statin therapy is used. Alternatively, selective use of statins with favorable effects on glucose metabolism may represent a feasible and safe strategy for managing these patients. Given recent reports indicating neutral or beneficial effects of pitavastatin on glucose metabolism [8, 9], pitavastatin is suggested as the preferred agent. However, the current clinical guidelines do not recommend a specific statin type in populations at high risk for developing NOD [1, 27], owing to the limited data available. Specifically, most previous studies had a fixed follow-up period of 12 weeks [7, 9], allowing only for assessment of the short-term effects of statins on glucose metabolism. More importantly, to date, there have been no clinical trials specifically designed to investigate the diabetogenic effects of statins. In this regard, a randomized trial with longer follow-up is warranted, considering that the long-term effect of statins on diabetes risk is a more clinically relevant endpoint. The LESS-DM trial will provide data on whether long-term use of pitavastatin (24 months), in comparison with atorvastatin (a representative diabetogenic statin), results in protective or deleterious effects on several parameters related to glucose metabolism in the setting of MetS. Thus, the findings of the LESS-DM trial will not only confirm or refute the previous observations regarding the favorable effects of pitavastatin on glucose metabolism but also extend knowledge about the long-term effects of intensive statin treatment on NOD.

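### All 500 randomised are said to be analysed, but 10% dropout is expected and the named primary tests need a 24-month HbA1c, so as stated they use about 450 people and not the 12-month value

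*Protocol article*

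**What the plan says.** All places are in the protocol article.

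- **Sample size.** The calculation includes "a presumed dropout rate of 10" percent and concludes that "a sample of 250 patients in each group will be sufficient to detect this difference". The next sentence reads: "Accordingly, a total of 500 participants will be randomized and included in our analysis".
- **Statistical analyses, sets.** "The intention-to-treat analyses will include all randomized participants who provide written informed consent", and this is the basis for the main analyses. Participants who complete the trial with adequate drug intake form a separate, per-protocol set.
- **Measurements.** The primary endpoint is the change in HbA1c after 24 months.
- **Statistical analyses, methods.** Between-group differences in change are tested by Student's t test and by "analysis of covariance to adjust for the baseline values". No repeated-measures model or imputation is named.
- **Table 1.** HbA1c is measured at baseline, 12 months and 24 months.

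**The concern.** A participant with no 24-month HbA1c has no change score. The t test and the ANCOVA, as named, cannot include that person unless the value is imputed or modelled. The statement that 500 are analysed, the 10% dropout and the named tests therefore fit together only with a step that the article does not state.

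Two things are at stake. One is precision. The other is bias, if those without a 24-month value differ from the rest in a way that depends on treatment. Such a difference is conceivable here. Treatment is open-label, the Discussion presents atorvastatin as typical of the statins that raise diabetes risk, and a 12-month HbA1c is measured halfway through follow-up. For anyone who leaves after month 12, that value is the best available information on the missing outcome, and neither named test uses it.

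**Working it through.** **1. The plan's own figure.** Stated inputs: difference 0.2, two-sided α 5%, power 95%, dropout 10%, 'variance' 0.5. With n per arm = 2·SD²·(1.960 + 1.645)²/0.2²:

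| Reading of 0.5 | n per arm | n/(1 − 0.10) |
|---|---|---|
| SD = 0.5 | 163 | 182 |
| variance = 0.5 (SD 0.707) | 325 | 362 |

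Neither reading gives 250. That is a separate issue, but it means that both SDs have to be carried through below.

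**2. How many people the named tests use.** If every dropout lacks the 24-month value, 500 × 0.90 = 450 have a change score (225 per arm) and 50 do not.

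**3. Loss of precision if dropout is unrelated to HbA1c.** The standard error grows by √(500/450) = 1.054, about 5%. Power = Φ(0.2/(SD·√(2/n)) − 1.960):

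| SD | 250 per arm | 225 per arm |
|---|---|---|
| 0.5 | 99.4% | 98.9% |
| 0.707 | 88.5% | 85.1% |

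The estimated difference stays at 0.20.

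**4. Bias if dropout is related to HbA1c.** In an arm with a fraction d missing, the observed mean differs from the true arm mean by −(d/(1 − d))·Δ. Here Δ is how far the missing people's 24-month change lies above the arm mean. With d = 0.10 the factor is 1/9. A bias of 0.02 therefore needs Δ = 0.18, and a bias of 0.04 needs Δ = 0.36.

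To see which Δ might arise, dropout was simulated with inputs that are assumptions and are not in the article: true difference 0.20; 10% dropout per arm; dropout in the atorvastatin arm only rising with the 12-month change, at a log-odds of 0.7 to 1.0 per SD; correlation 0.6 between 12- and 24-month changes.

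| SD | Log-odds 0.7 | Log-odds 1.0 |
|---|---|---|
| 0.5 | about 0.18 | about 0.17 |
| 0.707 | about 0.17 | about 0.16 |

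Entries are the difference estimated from people with a 24-month value. With log-odds 0 the estimate is 0.20.

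**5. What the 12-month value recovers.** Regressing the 24-month change on the 12-month change within arm and averaging over everyone returns 0.20, provided that every dropout has a 12-month value. If half of the dropouts leave before month 12, the estimate is about 0.18 to 0.19.

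**6. Effect on power in the biased case, 225 per arm.** SD 0.5, estimate 0.172: 0.172/0.0471 − 1.960 = 1.69, power about 95%. SD 0.707, estimate 0.165: 0.165/0.0667 − 1.960 = 0.515, power about 70%, against 85% without bias.

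**The case against.** The strongest reply is that this is missing-data handling, which a condensed article normally leaves to the full protocol or analysis plan. Inflating for dropout protects power and including all 500 describes the analysis set, so the two statements can stand together. A t test or ANCOVA can follow multiple imputation that uses the 12-month value. Much of this stands, and it rules out several stronger readings that a reader might infer:

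- *That intention-to-treat here is really a completer analysis.* The article defines the set as all randomised and keeps completers for the per-protocol set.
- *That the 12-month HbA1c is discarded.* The named primary tests do not use it, but the article does not say that it is excluded. It can also serve the new-onset diabetes endpoint, because an HbA1c threshold is one of the diagnostic criteria.
- *That patients who stop the drug are lost.* Those who stop but give the 24-month sample stay in. Bias requires the sample itself to be missing.
- *That 12-month results prompt patients to leave.* The laboratory section says that these assays are run as patients present, unlike the batched adiponectin. It does not say that results are reported to patients or acted on.

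The size of any bias also rests entirely on assumed inputs.

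The reply does not remove the mismatch. The article goes beyond silence: it gives a count of people analysed and names the tests, and without a further step those tests do not deliver that count.

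**Conclusion.** The point holds as a mismatch between a stated count and stated methods, with a better use of scheduled data available. It is not evidence that the trial will be biased.

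As stated and without imputation, the primary tests use about 450 of 500 people, assuming that every dropout lacks the 24-month sample. If dropout is unrelated to HbA1c there is no bias, and the loss of power is 0.5 percentage points (SD 0.5) or 3.4 points (SD 0.707). If dropout follows the 12-month change in the atorvastatin arm only, under the assumptions above, a true 0.20 is estimated at about 0.16 to 0.18. That bias is towards the null, so this scenario would understate an advantage of pitavastatin and would not create one. The same dependence in both arms would cancel. Worth correcting, with medium confidence in its practical importance.

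**What to change.** 1. Restate the closing sentence of the sample-size section along these lines: *500 will be randomised; about 450 are expected to have a 24-month HbA1c.*
2. Name a primary intention-to-treat analysis that uses the 12-month HbA1c. Either of these would do:
   - a mixed model for repeated measures at 12 and 24 months, with treatment by visit, baseline HbA1c by visit and the stratification factors (gender, previous statin use), and the 24-month contrast as the primary result;
   - the ANCOVA already planned, after multiple imputation within arm that includes the 12-month value.
3. Seek the already scheduled 24-month blood sample from participants who stop the study drug. This is the only step that helps with those who leave before month 12.

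If the full protocol or analysis plan already contains such a method, the first item and a cross-reference are enough.

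The cost is wording; no assessment is added. The downside is a missing-at-random assumption given the 12-month value. It is weaker than what an unimputed test needs, namely that dropout is unrelated to the outcome given arm and, for the ANCOVA, baseline.

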### Statistical analyses

The statistical analyses will be performed on both intention-to-treat and per-protocol bases. The intention-to-treat analyses will include all randomized participants who provide written informed consent, regardless of whether the study treatment is administered correctly. The per-protocol analyses will include all study participants who complete the trial with an adequate administration of the study drug (≥70% of the planned doses) and without any major protocol violations. Major protocol violations include inappropriate enrollment, the use of a prohibited concomitant medication, a violation of the dose or schedule of drug administration, or any other violation considered to be a major violation. The main analyses will be performed on an intention-to-treat basis.

The values will be expressed as the mean ± SD or median (IQR), as appropriate. Comparisons of continuous and categorical data will be made by Student’s *t* test and the chi-square test, respectively. The difference in changes between the groups will be analyzed using both Student’s *t* test and analysis of covariance to adjust for the baseline values. Two-sided *p* values < 0.05 will be considered statistically significant. All analyses will be performed using IBM SPSS version 22.0 software (IBM, Armonk, NY, USA).

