**Methods/design:**

The Long-term Effects of high-doSe pitavaStatin on Diabetogenicity in comparison with atorvastatin in patients with Metabolic syndrome (LESS-DM) trial is a prospective, randomized, open-label, active control clinical trial of patients with MetS. We plan to randomize 500 patients with MetS (1:1) to receive high-dose pitavastatin (4 mg) or atorvastatin (20 mg) daily for 24 months. The primary endpoint will be the change in hemoglobin A1c after statin treatment. Secondary endpoints will include the following: (1) changes in biochemical markers, including insulin, C-peptide, homeostasis model assessment of insulin resistance and insulin secretion, and adiponectin; (2) changes in imaging parameters, including carotid elasticity metrics and indices of cardiac function; and (3) the incidence of clinical events, including new-onset diabetes and cardiovascular disease.

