### Interventions

The trial will be conducted for 24 months. After randomization, the study participants will take pitavastatin 4 mg or atorvastatin 20 mg once daily. The prescription and administration of the study medications will be performed in an open-label manner. The dose of pitavastatin was set on the basis of a previous study in which researchers reported the effect of high-dose pitavastatin on glucose homeostasis [8]. Atorvastatin was chosen as the active control because it is the most commonly used statin and has been reported to result in an increase in insulin resistance and ambient glycemia [17]. The dose of atorvastatin was selected on the basis of previous experiments comparing these two statins [18, 19]. The investigators and clinical research coordinators will assess the drug compliance of the study participants, and those with < 70% compliance will be excluded from the per-protocol analysis. In addition to medical interventions, lifestyle modifications will be encouraged as background therapy in this study. On the basis of previous studies, the patients’ smoking status, alcohol consumption, diet, and level of physical activity are considered major modifiable lifestyle factors [20, 21]. Thus, the patients will be instructed and encouraged to adhere to healthy lifestyles, including not smoking, no excessive alcohol consumption, low-risk diets, and being physically active.

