In addition, the incidences of NOD and CVD, including coronary heart disease (angina, myocardial infarction, cardiac revascularization, or coronary death), stroke (fatal or nonfatal ischemic stroke), heart failure, arrhythmia, peripheral vascular disease, and venous thromboembolism, will be assessed during the follow-up of this trial. Follow-up of these clinical events will be performed by means of in-office visits, medical record review, and telephone contact. Specifically, trained research personnel who are unaware of the study group assignments will review all medical records and will also conduct telephone interviews if needed to monitor the development of clinical events. The schedule for the assessments is summarized in Table 1.

**Table 1 Tab1:** Schedule of study assessments

	V1 (Baseline)	V2 (6 months)	V3 (12 months)	V4 (18 months)	V5 (24 months)
Informed consent	√				
Medical history	√	√	√	√	√
Physical examination	√	√	√	√	√
Vital signs	√	√	√	√	√
Anthropometric measures	√		√		√
Blood tests					
Complete blood count	√				√
Routine blood chemistry	√		√		√
Lipid profile	√		√		√
Fasting plasma glucose	√		√		√
Hemoglobin A1c	√		√		√
Insulin	√		√		√
C-peptide	√		√		√
HOMA-R	√		√		√
HOMA-β	√		√		√
Adiponectin	√		√		√
High-sensitivity CRP	√				√
Cardiac troponin I	√				√
Creatine kinase	√		√		√
Carotid ultrasound					
Strain by B-mode	√		√		√
Stiffness by B-mode	√		√		√
Distensibility by B-mode	√		√		√
Strain by speckle tracking	√		√		√
Stiffness by speckle tracking	√		√		√
Echocardiography					
2D measurements	√		√		√
M-mode parameters	√		√		√
Doppler parameters	√		√		√
Tissue Doppler parameters	√		√		√
2D speckle-tracking analysis	√		√		√
Clinical events	√	√	√	√	√

*Abbreviations: HOMA-R* Insulin resistance index of homeostasis model assessment, *HOMA-β* Secretory ability of homeostasis model assessment, *CRP* C-reactive protein, *2D* Two-dimensional

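### The single per-protocol set requires completing the trial, so fatal cardiovascular events can never appear in a per-protocol comparison of clinical events

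*Protocol article*

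**What the plan says.** The Statistical analyses section opens with a general statement: "The statistical analyses will be performed on both intention-to-treat and per-protocol bases". No endpoint is exempted. It then defines one per-protocol set: "The per-protocol analyses will include all study participants who complete the trial with an adequate administration of the study drug". The same sentence adds the remaining conditions: "≥70% of the planned doses) and without any major protocol violations". A violation of the dose or schedule of study drug is among the listed major violations. The section also ranks the two sets: "The main analyses will be performed on an intention-to-treat basis".

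The Interventions section repeats the dose threshold ("those with < 70% compliance will be excluded from the per-protocol analysis") and sets the length of the study: "The trial will be conducted for 24 months".

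The Methods/design paragraph of the Abstract lists, as the third group of secondary endpoints, "the incidence of clinical events, including new-onset diabetes and cardiovascular disease". The Measurements section says what counts as cardiovascular disease, beginning with "coronary heart disease (angina, myocardial infarction, cardiac revascularization, or coronary death), stroke (fatal or nonfatal ischemic stroke), heart failure". Two of these components are deaths: coronary death and fatal ischaemic stroke.

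**The concern.** A completer set is a natural choice for the change in HbA1c at month 24, because that endpoint exists only for participants measured at month 24. It does not suit an endpoint that counts events during follow-up. There, some of the events themselves prevent completion, so membership of the set depends on the outcome being compared.

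At stake is what a per-protocol table of clinical events would mean. It would describe survivors only, with the fatal components empty in both arms whatever happened in the trial. Set beside the intention-to-treat table, it could seem to confirm or contradict the main result for a reason unrelated to adherence. The trial is open-label and the authors expect few events, so a handful of removed events could noticeably change the picture.

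**Working it through.** The article gives no figure to reproduce on this point. The check compares the membership rule with the endpoint definition and adds simple arithmetic.

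**Inputs from the article**
- Trial length: 24 months (Interventions).
- Membership: completes the trial, takes at least 70% of planned doses, has no major violation (Statistical analyses).
- Fatal events counted: coronary death and fatal ischaemic stroke (Measurements).
- Method named for categorical data: chi-square test (Statistical analyses). It compares proportions within the set, so a participant outside the set contributes neither an event nor a denominator.
- Event rates, share of events that are fatal, share followed by stopping study drug: not given.

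**Step 1: fatal events**
- Death at month 10: 10/24 = 41.7% of planned doses at most. The participant fails both the completion condition and the dose condition.
- Death at month 20 with full adherence: 20/24 = 83.3% of planned doses. The dose condition is met, but the completion condition is not.

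The completion condition alone therefore removes 100% of deaths before month 24. This needs no assumption about rates. The dose condition, if planned doses means the full 24 months of doses, independently removes deaths before 0.70 × 24 = 16.8 months. Deleting the completion requirement would therefore not be enough; the dose denominator must also end at the event.

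**Step 2: non-fatal events after which study drug is stopped for good**

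With full prior adherence, stopping before month 16.8 leaves less than 70% of planned doses, and the participant is out even if followed to month 24. Stopping after month 16.8 gives no clear answer, because the article does not say whether completing the trial means completing follow-up or completing treatment.

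**Step 3: how large it could be (illustration only)**

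Let f be the share of cardiovascular events that are fatal, and s the share of non-fatal events after which drug is permanently stopped. Neither is in the article. Assume f = 5% to 30%, s = 10% to 50%, and event times spread evenly over 24 months.
- Dose condition only for non-fatal events: share removed = f + (1 − f) × s × 0.70. With f = 0.05 and s = 0.10: 0.05 + 0.95 × 0.10 × 0.70 = 0.1165, about 12%.
- Stopping drug treated as not completing: share removed = f + (1 − f) × s. With f = 0.30 and s = 0.50: 0.30 + 0.70 × 0.50 = 0.65, or 65%.

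The width of that range shows that the article does not fix the size.

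**Step 4: what removing deaths alone can do (invented counts)**

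Suppose 10/250 = 4.0% and 15/250 = 6.0% have an event, of which 1 and 5 are fatal. Removing only the fatal cases gives (10 − 1)/(250 − 1) = 9/249 = 3.6% and (15 − 5)/(250 − 5) = 10/245 = 4.1%. The gap falls from 2.0 to about 0.5 percentage points. The uneven split of deaths was chosen to show the mechanism and is not a forecast.

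**The case against.** The strongest reply is that little depends on this analysis. Intention-to-treat is the main analysis, includes all randomised participants and keeps every fatal event. The endpoint is secondary, and the Strengths and weaknesses section concedes that the sample is small for clinical outcomes. That reply stands and limits the importance of the point. A reader might infer that any difference between the arms in these events would be hidden. It would not be, because the intention-to-treat comparison shows it.

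A second reply is that no sentence promises a per-protocol comparison of cardiovascular events; it is inferred from the general opening sentence of Statistical analyses, and a full protocol or analysis plan could narrow it. The inference must be acknowledged. Still, the sentence is unrestricted and a single membership rule follows it. The criticism is of that stated rule, not of missing detail.

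A third reply concerns non-fatal events. A reader might infer that many infarctions, strokes or heart failure episodes would be lost because treatment ends. The article does not support this. It nowhere says that such an event leads to stopping or changing the study statin, nor that a clinically directed change counts as a dose violation, and it gives no rates. Exclusion by definition applies strictly to deaths only.

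A reader might also infer that treating new-onset diabetes would itself count as use of a prohibited medication and remove the participant. The article bars drugs affecting glucose metabolism at enrolment but does not list what is prohibited during follow-up, so this cannot be claimed.

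**Conclusion.** The point holds for deaths, and for a supportive analysis of a secondary endpoint. As the article stands, every coronary death and fatal ischaemic stroke before month 24 is outside the per-protocol set. This conclusion rests on two readings: that the opening sentence on analysis bases covers clinical events, and that someone who dies has not completed the trial. The first is an inference from unrestricted wording; the second is hardly open to doubt.

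For non-fatal events, loss is possible when drug is stopped before about month 16.8, but its frequency is unknown. The 12% to 65% range depends entirely on assumed shares and should not be cited as an estimate. The main conclusions on HbA1c and the intention-to-treat event results are unaffected. The correction is still worth making, because a comparison in which the fatal components cannot occur has no useful interpretation.

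**What to change.** State in Statistical analyses that the completer-based per-protocol set applies to the month-24 continuous endpoints only. For clinical events (cardiovascular disease and new-onset diabetes), choose one of two rules in advance:

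1. Analyse by intention-to-treat only. This takes one sentence and no further work.
2. Define a separate per-protocol set for events with no completion requirement. Judge adherence against the doses planned up to the first event or death, and count violations only up to that point, so that nobody is excluded because the event occurred.

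Option 2 costs a second per-protocol definition and slightly more analysis work, and it needs adherence to be known up to the event date. It still selects on behaviour after randomisation: someone with an early event has had less time to fall below the adherence threshold than someone followed for 24 months. It should remain supportive. An on-treatment analysis that stops counting at a fixed lag after the last dose is another possibility, but its censoring can itself be informative and it is not needed to cure this defect. Intention-to-treat remains the main analysis in every case.
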